# Protocol for a multicenter, randomized, single-blind, non-inferiority trial comparing nalbuphine hydrochloride versus hydromorphone hydrochloride for analgesia in mechanically ventilated ICU patients

**DOI:** 10.3389/fphar.2026.1795531

**Published:** 2026-04-28

**Keywords:** analgesia, hydromorphone hydrochloride, intensive care, mechanical ventilation, nalbuphine hydrochloride

## Abstract

**Introduction:**

Despite the established use of nalbuphine hydrochloride in anesthesia and obstetrics, high-quality evidence supporting its application in the intensive care unit (ICU) remains limited. This study aims to assess the efficacy and safety of nalbuphine hydrochloride for analgesia in ICU patients.

**Methods:**

This is a multicenter, randomized, single-blind, parallel, positive control study. Eligible patients are randomly assigned to receive nalbuphine hydrochloride or hydromorphone hydrochloride in a 1:1 ratio. Nalbuphine hydrochloride is compared against hydromorphone hydrochloride which serves as the positive control. The study drug infusion is discontinued after 24 h (±10 min) of administration.

**Planned Outcomes:**

The primary outcome is the analgesic success rate during 24 h of study drug administration. The secondary outcomes include the following: 1) The percentage of time within CPOT score ≤2 and RASS score between −2 and +1 during 24 h of study drug administration. 2) The frequency and dosage of rescue sedation during 24 h of study drug administration. 3) The proportion of patients requiring rescue sedation during 24 h of study drug administration. 4) The total cumulative dose of rescue sedative during 24 h of study drug administration. 5) The time to successful weaning and ICU discharge during 24 h of study drug administration. 6) The weaning success rate and the proportion of patients discharged from the ICU.

**Clinical Trial Registration:**

https://clinicaltrials.gov/ct2/show/NCT06785571, identifier NCT06785571.

## Introduction

Effective analgesia and sedation are central to the management of critically ill patients, not only to alleviate pain and distress but also to facilitate tolerance of invasive procedures, optimize ventilatory synchrony, and prevent the harmful physiological consequences of uncontrolled nociception. Current international guidelines consistently endorse an “analgesia-first” or “analgosedation” approach, emphasizing that adequate pain control should form the foundation upon which sedation strategies are built—particularly for managing anxiety and achieving amnesia when necessary (Devlin et al., 2018; Barr et al., 2013; Vincent et al., 2016; Society Of Critical Care Medicine Chines e Medical A, 2018). Within this framework, the selection of an appropriate analgesic agent is critical, requiring careful consideration of efficacy, safety, and predictable pharmacokinetics in the context of the unstable physiology commonly seen in intensive care unit (ICU) patients.

Among available pharmacological options—including opioids, non-opioid central analgesics, nonsteroidal anti-inflammatory drugs, and local anesthetics—nalbuphine hydrochloride exhibits a particularly distinctive pharmacological profile. Developed by DuPont in 1965 and approved for clinical use in the United States in 1979 under the brand name Nubain®, nalbuphine hydrochloride acts as a κ-opioid receptor agonist and μ-opioid receptor antagonist (Schmidt et al., 1985). Its dual mechanism provides effective analgesia while demonstrating a ceiling effect on respiratory depression, along with favorable hemodynamic stability and a low potential for abuse (Schmidt et al., 1985; Mathai et al., 2019). Clinically, nalbuphine hydrochloride has been widely used for the management of moderate to severe pain (Schnabel et al., 2014), as an adjunct in perioperative anesthesia (Kubica-Ciel et al., 2015; Liu et al., 2022), and as a safe and effective analgesic during labor (Vavri et al., 2005). Given these characteristics, nalbuphine hydrochloride represents a theoretically favorable alternative in clinical settings where the limitations of conventional opioids are of significant concern—particularly among critically ill patients.

Indeed, although traditional opioids remain mainstays of analgesic therapy in the ICU, they are associated with notable adverse effects. Dose-dependent respiratory depression poses ongoing risks even in mechanically ventilated patients, suppression of gastrointestinal motility may delay recovery, and growing evidence links their use to long-term dependence and increased cumulative opioid exposure (Devlin et al., 2018; Müller-Lissner et al., 2017; Donohue et al., 2019). These drawbacks highlight the need for viable therapeutic alternatives. Nalbuphine may offer a favorable safety profile in ICU patients due to the above advantages. However, high-quality clinical data supporting its use specifically in ICU patients remain limited. Critical illness frequently alters drug absorption, distribution, metabolism, and excretion (Chen and Huang, 2024), and analgesic requirements in this population may differ significantly from those observed in surgical or obstetric cohorts, thus necessitating targeted evaluation. To address these evidence gaps, we conduct a clinical study to evaluate the efficacy and safety of nalbuphine hydrochloride for analgesia in ICU patients. To rigorously evaluate its role, hydromorphone hydrochloride, a potent μ-opioid agonist widely used in critical care analgesia (Liu and Gropper, 2003), was selected as the positive control to determine whether nalbuphine can provide non-inferior analgesia while reducing the adverse effects commonly associated with traditional opioids. Collectively, our study provides essential evidence for nalbuphine’s potential role in critical care analgesia.

## Methods

### Study design

This is a multicenter, randomized, single-blind, parallel, positive control study initiated by Yichang Humanwell Pharmaceutical Co., Ltd., China. Apart from our ICU, 15 ICUs from tertiary hospitals in China enroll patients in the trial. This study was registered at ClinicalTrials.gov (NCT06785571). The trial protocol is reported in accordance with the Standard Protocol Items: Recommendations for Interventional Trials (SPIRIT) guidelines (Calvert et al., 2018). Table 1 presents the scheduled process of enrollment, interventions, and measurements.

**TABLE 1 T1:** Scheduled process of enrollment, interventions, and measurements.

Timepoint	Study period				
	Enrollment	Allocation	Post-allocation		Close-out
	After admission to ICU	After obtaining informed consent	Before study drug administration	Study drug administration	12–48 h after study drug administration ended
Enrollment					
Eligibility screen	X	​	​	​	​
Informed consent	X	​	​	​	​
Allocation	​	X	​	​	​
Interventions					
Nalbuphine hydrochloride	​	​	​	X	​
Hydromorphone hydrochloride	​	​	​	X	​
Assessments					
Baseline variables	X	​	​	​	​
Vital signs	X	X	X	X	X
RASS score	X	X	X	X	​
CPOT score	X	X	X	X	​
Laboratory tests	X	​	​	​	X
APACHE II score and SOFA score					
Dose of drugs (study drugs, analgesics, vasopressors, rescue sedatives)	​	​	​	X	​
AEs and SAEs	​	​	​	X	​
Outcome variables	​	​	​	​	X

RASS, Richmond Agitation–Sedation Scale; AEs, adverse events; SAEs, serious adverse events.

### Participants

Inclusion criteria are: 1) age ≥18 years and ≤80, 2) ICU patients who are intubated are expected to require mechanical ventilation for more than 6 h, 3) patients or their guardians have a full understanding of the purpose and significance of this trial, and voluntarily participate in this clinical trial and sign an informed consent form.

Exclusion criteria are: 1) allergy or unsuitability to any composition of study drugs or propofol, 2) life expectancy of less than 48 h, 3) neurological disorder and any other condition interfering with sedation assessment, 4) gastrointestinal obstruction, 5) asthmatic, 6) abdominal compartment syndrome, 7) serious hepatic dysfunction (Child-Turcotte-Pugh score 10–15), 8) acute kidney injury (KDIGO stage 2 or 3) or chronic kidney disease with glomerular filtration rate (GFR) < 29 mL/min/1.73 m^2^, 9) circulatory instability (the need for a continuous infusion of norepinephrine at ≥ 0.5 ug/kg/min to maintain proper blood pressure), 10) a need of deep sedation (RASS score −4 or −5) or paralytics, 11) anticipation to receive operations (including tracheotomy), 12) abuse of controlled substances or alcohol, 13) pregnancy, lactation, or an intention of gestation in 6 months, 14) inclusion in another interventional trial in the past 30 days, 15) other conditions deemed unsuitable to be included.

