### Intervention

Analgesics and sedatives administered prior to enrollment are discontinued. In the experimental group, patients receive intravenous nalbuphine hydrochloride (Yichang Humanwell Pharmaceutical Co., Ltd., China). A loading dose of 6 mg nalbuphine Hydrochloride is administered over 30 s (±10 s), followed immediately by initiation of a continuous maintenance infusion at a baseline rate of 2.0 mg/h. Five minutes after the loading dose, if the patient’s Critical-Care Pain Observation Tool (CPOT) score is greater than 2, a 2 mg supplemental bolus is given. This supplemental bolus may be repeated once, with a minimum interval of 5 min between doses, allowing up to two supplemental boluses within the first 20 min. The total dose, including the loading dose and any supplemental boluses, is capped at 10 mg, and no additional boluses are permitted beyond the initial 20-min period. Twenty minutes after the loading dose or once the cumulative dose reaches 10 mg, the maintenance infusion rate is titrated according to CPOT and Richmond Agitation-Sedation Scale (RASS) scores. Dose adjustments are made in increments of 0.5 mg/h, within a target range of 1.0–5.0 mg/h, with a minimum of 5 min between each adjustment. In the control group, patients receive hydromorphone hydrochloride (Yichang Humanwell Pharmaceutical Co., Ltd., China) via continuous intravenous infusion, initiating at 0.5 mg/h. The infusion rate is adjusted based on CPOT and RASS scores in increments of 0.5 mg/h within a target range of 0.5–3.0 mg/h, with at least 5 min between adjustments.

If a patient’s CPOT score remains above 2 despite reaching a nalbuphine infusion rate of 3.0 mg/h or a hydromorphone hydrochloride infusion rate of 2.0 mg/h, rescue sedation with propofol is initiated. Propofol is started at an initial infusion rate of 0.5 mg/kg/h and subsequently titrated in increments of approximately 25% of the current rate (0.125 mg/kg/h), within a dosage range of 0–4 mg/kg/h.

The study drug infusion is discontinued after 24 h (±10 min) of administration or earlier if the patient met weaning criteria and a spontaneous breathing trial is planned. Patients requiring ongoing analgesia or sedation after discontinuation of study drugs are managed at the investigator’s discretion.

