### Outcomes

The primary outcome is the analgesic success rate during 24 h of study drug administration. Analgesic success is defined as the fulfillment of both criteria: 1) no administration of rescue analgesic medication, and 2) maintenance of a CPOT score ≤2 for at least 70% of the observation period during study drug infusion.

The secondary outcomes include: 1) The percentage of time within CPOT score ≤2 and RASS score between −2 and +1 during 24 h of study drug administration: This metric represents the proportion of time during which a patient maintains a CPOT score of ≤2 and a RASS score between −2 and +1, relative to the total duration of study drug administration. 2) The frequency and dosage of rescue sedation during 24 h of study drug administration: The frequency refers to the number of rescue sedative administrations, while the dosage indicates the total amount of propofol administered as rescue sedation during the infusion of the study drug. 3) The proportion of patients requiring rescue sedation during 24 h of study drug administration: This is the percentage of patients in each treatment group who received concomitant propofol for rescue sedation during study drug infusion, calculated as (Number of patients receiving propofol/Total number of patients in the group) × 100%. 4) The total cumulative dose of rescue sedative during 24 h of study drug administration: The sum of all propofol doses administered as rescue sedation during the period of study drug infusion. 5) The time to successful weaning and ICU discharge during 24 h of study drug administration: Time to successful weaning is defined as the interval from the initiation of the study drug to liberation from mechanical ventilation. Time to ICU discharge is defined as the interval from study drug initiation to actual ICU discharge. Successful weaning is achieved when the patient is extubated and subsequently maintains stable spontaneous breathing without the need for reintubation. 6) The weaning success rate and the proportion of patients discharged from the ICU: The weaning success rate reflects the percentage of patients successfully weaned from mechanical ventilation. The proportion of patients discharged from the ICU indicates the percentage of patients transferred out of the ICU within the observation period.

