### Data collection and management

Upon enrollment, detailed patient demographic data (age, sex, body weight, ethnicity), medical history, clinical data (vital signs, ECG, laboratory tests), and comorbidities are collected. Vital sign monitoring includes heart rate, systolic and diastolic blood pressure (SBP/DBP), respiratory rate, and peripheral capillary oxygen saturation (SpO2). These parameters are recorded immediately at the initiation of the study drug administration (designated as T0), with subsequent assessments performed every 20 min during the first 2 h post-administration. From 2 to 24 h post-administration, or when weaning screening criteria are met and a weaning trial is planned, recordings are taken every 2 h. Additional recordings are obtained immediately following successful weaning and/or ICU discharge. Body temperature is recorded at T0 and again at 24 h post-administration or when weaning criteria are met. Continuous ECG monitoring is conducted throughout the study drug administration. Standard 12-lead ECG is obtained, and blood samples (for complete blood count, biochemistry, coagulation profile, and pregnancy test when applicable) are collected before randomization and within 12–48 h after discontinuation of the study drugs.

The CPOT and RASS scores are evaluated as baseline assessments prior to randomization. Routine evaluations are performed immediately after T0 and every 2 h thereafter. Prior to any dose adjustment, both scores are documented. After each adjustment, assessments are repeated every 5 min until clinical targets are met and no further dose modifications are needed. If the patient is in undisturbed sleep, the RASS score is recorded as unchanged from the previous value and annotated as “sleeping”. However, for final determination of titration cessation, patients are awakened for formal CPOT and RASS evaluation.

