### Estimation of sample size

The sample size estimation is based on a non-inferiority design. According to previous findings and literature reports (Liu et al., 2018), nalbuphine is capable of maintaining the target analgesic effect within 3–24 h post-administration, with CPOT scores ≤2 for more than 70% of the time. An analgesic success rate approaching 100% is anticipated. We estimate an efficacy of 99% in the experimental group, and the control groups. Following consultation of several experts, the non-inferiority margin δ is set at −8%, meaning that an 8% reduction in efficacy representing the maximum clinically acceptable difference. A two-sided significance level of α = 0.05 and a power of 80% (β = 0.2) are applied. Sample size estimation is conducted using the Farrington and Manning method via PASS 2022 software, assuming a 1:1 allocation ratio between the two groups, and 73 participants per group is required. Assuming an anticipated dropout rate of approximately 12%, a total of 168 subjects is needed.

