### Statistical analysis

Statistical analyses will be performed using SAS software (version 9.4 or higher). Continuous variables will be presented as mean ± standard deviation for normally distributed data and median ± interquartile range for non-normally distributed data, whereas categorical variables will be summarized as frequencies and percentages. All statistical tests and confidence intervals (CI) will be two-sided, with statistical significance defined as a p-value less than 0.05. The difference in analgesic success rates between the experimental and control groups will be estimated using the Miettinen and Nurminen method to calculate the two-sided 95% CI. Non-inferiority will be established if the lower bound of this interval exceeds −8%. The proportion of time during which patients maintain a CPOT score ≤2 and a RASS score between −2 and +1 will be analyzed using the arcsine square root transformation, followed by between-group comparison via the t-test. Time from initiation of study drug to successful weaning and time to ICU discharge will be illustrated using Kaplan-Meier survival curves and compared using the log-rank test. The frequency and dosage of rescue propofol sedation, along with total propofol dose administered, will be compared between groups using either the t-test or Wilcoxon rank-sum test, depending on data distribution. The proportions of patients requiring concomitant propofol sedation, weaning success rate, and ICU discharge rate will be compared using the χ^2^ test or Fisher’s exact test. The incidence of adverse events will also be assessed using χ^2^ test or Fisher’s exact test.

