
To maximize clinical utility, prespecified subgroup and sensitivity analyses are necessary. Subgroup analyses stratified by baseline hepatic function (e.g., Child-Pugh class) and renal function (e.g., KDIGO stage) would assess whether nalbuphine’s noninferiority is maintained across the spectrum of organ dysfunction severity. Sensitivity analyses adjusting for key potential confounders—including illness severity (e.g., APACHE II score), concomitant sedative use, and delirium status—would further enhance the robustness and generalizability of the primary findings. Although these analyses are exploratory, they are valuable for generating new research ideas and guiding personalized pain management in critically ill patients.

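### No pain or analgesic-need criterion at entry, with near-100% success expected, lets patients who would succeed on either drug dilute the difference towards non-inferiority; assay sensitivity is not established

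*Protocol article*

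**What the plan says.** All references are to the protocol article.

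- **Participants.** The inclusion criteria are age, consent and the condition that "ICU patients who are intubated are expected to require mechanical ventilation for more than 6 h". None of the 3 inclusion or 15 exclusion criteria mentions pain, CPOT or a need for an opioid.
- **Intervention.** "Analgesics and sedatives administered prior to enrollment are discontinued".
- **Outcomes.** Analgesic success needs no rescue analgesic and "maintenance of a CPOT score ≤2 for at least 70% of the observation period during study drug infusion".
- **Data collection and management.** "The CPOT and RASS scores are evaluated as baseline assessments prior to randomization".
- **Estimation of sample size.** "An analgesic success rate approaching 100% is anticipated", and "We estimate an efficacy of 99% in the experimental group, and the control groups". The margin of −8 points comes from expert consultation. No success rate without an opioid is given.
- **Statistical analysis.** The difference in success rates is "estimated using the Miettinen and Nurminen method to calculate the two-sided 95% CI", and its lower bound must exceed −8%. No baseline term or stratum is named. Time in target is compared by a t-test after an arcsine square root transformation, without baseline scores.
- **Limitations.** Adjusted sensitivity analyses are suggested for confounders "including illness severity (e.g., APACHE II score), concomitant sedative use, and delirium status". Baseline pain is not among them, and the lack of a pain criterion is not listed as a limitation.

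**The concern.** A non-inferiority trial without a placebo arm must rely on its design to show that it could have detected a worse drug. Here a patient with little pain can be enrolled and can meet the success definition whichever drug is infused. Each such patient adds a success to either arm and no information on the contrast, so the observed difference shrinks towards zero. In a superiority trial that would be conservative; here it favours the claim.

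The near-100% success rate expected in both arms makes the question pressing. It could mean that both drugs work very well, or that many enrolled patients would have succeeded anyway, and the document gives nothing to tell these apart. At stake is whether a positive result can be read as evidence about patients who need analgesia.

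**Working it through.** **1. The plan's own figure.** Farrington-Manning, 99% in both arms, margin −0.08, one-sided 0.025, power 80%. The restricted estimates under a difference of −0.08 are 0.9149 and 0.9949.

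- Null variance: 0.9149 × 0.0851 + 0.9949 × 0.0051 = 0.0829
- Alternative variance: 2 × 0.99 × 0.01 = 0.0198
- n = (1.960 × √0.0829 + 0.842 × √0.0198)² / 0.08² = 72.86, so 73 per arm, as stated
- Dropout: 73 / 0.88 = 82.95, so 83 per arm and 166 in all, against 168 stated. The gap of 2 is immaterial.

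At 99% success, 73 × 0.01 = 0.73 failures per arm are expected.

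**2. Dilution.** Let q be the share who would succeed on either drug (an assumption; not in the documents) and D the deficit of nalbuphine in the remaining patients, where control success is taken as 99%.

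- Overall control rate = q + (1 − q) × 0.99
- Overall nalbuphine rate = q + (1 − q) × (0.99 − D)
- Overall difference = −(1 − q) × D
- Deficit in the remaining patients that equals the margin overall = 8 / (1 − q) points

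The probability of declaring non-inferiority, P(NI), was obtained by summing the binomial probabilities of all outcomes with 73 per arm for which the Miettinen-Nurminen lower limit exceeds −8%. For D = 8 points:

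| q | Control overall | Nalbuphine overall | Difference | P(NI) | Deficit equal to margin |
|---|---|---|---|---|---|
| 0 | 99.0% | 91.0% | −8.0 | 1.5% | 8.0 |
| 30% | 99.3% | 93.7% | −5.6 | 6% | 11.4 |
| 50% | 99.5% | 95.5% | −4.0 | 17% | 16.0 |
| 70% | 99.7% | 97.3% | −2.4 | 42% | 26.7 |
| 80% | 99.8% | 98.2% | −1.6 | 62% | 40.0 |

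With 84 per arm (168 / 2) the probabilities are 1.8%, 7%, 17%, 40% and 59%.

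**3. What the trial can still detect** (73 per arm).

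- D = 20 points: P(NI) is 0.4% at q = 50% and 5% at q = 70%.
- Control at 99% overall and nalbuphine at 97%, 95%, 93% or 90% overall: P(NI) is 41%, 15%, 5% or 0.8%.

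An ineffective drug would therefore pass often only if roughly 95–97% or more of enrolled patients would succeed without it.

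**4. What a subset with baseline CPOT above 2 can show.** With no failures in either arm, the Miettinen-Nurminen lower limit is −k / (1 + k), where k = 2 × 1.96² / (2n − 1). If half the patients qualify (assumption), n is about 37 per arm: k = 7.683 / 73 = 0.1052 and the limit is −9.5%. At n = 44, k = 7.683 / 87 = 0.0883 and the limit is −8.1%; at n = 45, k = 7.683 / 89 = 0.0863 and it is −7.9%. A subset below 45 per arm cannot meet the margin even with no failures.

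**The case against.** The strongest reply has four parts.

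*The trial is not blind to inferiority.* A reader might infer that it lacks assay sensitivity. The documents do not support that: neither q nor the success rate without an opioid is given, and step 3 shows that large deficits are rejected almost always unless q is very high. A reader might also note that a 15-point deficit at q = 50% becomes −7.5 overall, and a 20-point deficit at q = 70% becomes −6, and call both inside the margin. But the decision uses the lower confidence limit, and these cases pass only about 2% and 5% of the time. This part stands.

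*A low baseline CPOT does not mean a patient cannot fail.* Earlier analgesics may still act when the score is taken and are then stopped, so need can emerge later. This stands. Baseline CPOT of 2 or less cannot be equated with q, and baseline CPOT is an imperfect marker of need.

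*The population is a legitimate choice.* The stated aim is analgesia in ventilated ICU patients, and for that whole population the test keeps its error rate: 1.5% at a true −8. The probabilities in step 2 are errors only if the 8-point limit is meant to hold for patients who need analgesia. This stands as to validity. It does not help a reader who wants to know whether nalbuphine relieves pain as well as hydromorphone.

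*Subgroups and covariates belong in the SAP, which is not shown.* Fair: silence on a baseline CPOT analysis does not prove that none is planned. But entry criteria, endpoint, expected rates, primary analysis and the t-test are all stated in the article, and the dilution follows from how the first three combine.

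Nor does leaving baseline CPOT out of the primary analysis cause the dilution. Stratifying the overall difference would still average over all enrolled patients.

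**Conclusion.** The point holds in a limited form. Entry does not select for pain or analgesic need, success near 100% is expected, and patients who would succeed on either drug move the difference towards non-inferiority. Assay sensitivity is not established; it is not shown to be absent.

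The size depends on q. The chance of accepting an 8-point deficit in the remaining patients stays at 6% or less up to q = 30%, and reaches 17% at 50% and 62% at 80%. This rests on control success of 99% in those patients, 73 analysed per arm and certain success in the share q. The sample size arithmetic itself is sound.

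**What to change.** Keep eligibility and sample size, and fix the following before unblinded data are seen.

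1. Prespecify the difference in success rates, with its Miettinen-Nurminen interval, in patients with baseline CPOT above 2, reported beside the overall result as supportive only. Make no non-inferiority claim for patients in pain unless this subset supports it, and state in advance what counts as support, because the −8% rule may be out of reach there (step 4).
2. Replace the plain t-test for time in target with a baseline-adjusted comparison: the transformed proportion regressed on treatment, baseline CPOT and baseline RASS. This uses data already collected and improves precision; it does not cure the dilution.
3. List among the limitations that entry requires no pain, and that baseline CPOT may reflect earlier analgesics.

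Stratifying the overall difference by baseline CPOT is optional and does not remove dilution.

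The cost is wording and a few extra analyses; the price is a wide interval in the subset. Restricting entry instead would reopen the 99% assumption: at the same margin and power, Farrington-Manning needs 146 per arm (332 in all after 12% dropout) at 95% success, and 235 per arm (536 in all) at 90%.
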